The outcome measure for pain will be the Pain, Enjoyment, and General Activity (PEG) scale, a 3-item commonly reliable and validated measure used in oncology populations that asks about pain severity, pain interference in enjoyment of life, and pain interference in general well-being [48-50]. The PEG meets the Initiative on Methods, Measurement, and Pain Assessment in Clinical Trials recommendations and has a 7-day recall period [51]. The PEG will be collected weekly to provide longitudinal impact on pain severity, pain interference, and whether opioids precede any change in pain.

Additional monthly PROs will include information on mood (Functional Assessment of Cancer Therapy-General Well-Being Subscale); comorbidities (Self-Administered Comorbidity Questionnaire); functioning (Carey index); and if prescribed opioids, information on opioid misuse (Patient-Reported Outcomes Measurement Information System), opioid side effects (Patient-Reported Outcomes version of the Common Terminology Criteria for Adverse Events), and substance use (Tobacco, Alcohol, Prescription Medication, and Other Substance Use Tool) [52-56]. These measures were selected because of their favorable psychometrics in the study population, brevity, and similar recall periods. This patient-participant burden is similar to other studies among patients with metastatic cancer [57].

For Aim 3, we will conduct one-on-one interviews with patients, their care partners, and clinicians with the goal of better understanding opioid-related decision-making. These interviews will occur every 3 months for 2 years or until death. The rationale for this frequency is that it strikes a balance between interviewing people often enough for them to remember aspects of opioid decision-making since the last interview but not so often as to ask about opioid-related decisions more frequently than those decisions occur or cause undue participant burden.

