### Analytic Plan

#### Aim 1: Data Analysis

This analysis will draw from all patient participants, regardless of whether they are prescribed opioids, so we can compare those who are with those who are not prescribed opioids. We will estimate differences in pain severity and interference between patients treated with opioids versus patients not treated with opioids using linear mixed-effects models, which will allow us to (1) account for repeated measures over time for each patient and (2) adjust for potential confounders. In the linear mixed-effects models, the dependent variables will be based on the PEG: pain severity (first question is a continuous 0-10 value) and pain interference (mean of 3 PEG items) at each time point. Current opioid prescription, baseline pain severity or interference, and other confounders (ie, factors statistically associated with the exposure and outcome) will be included as fixed effects, while the subject will be included as a random effect.

#### Power Calculation for Aim 1

Power calculations were performed by simulation to allow a range of parameters to vary in all scenarios. Unlike a randomized trial, in this study we will not have control over the ratio of patients allocated to the 2 comparison groups (eg, there will not be precisely a 1:1 ratio of patients prescribed opioids vs patients not prescribed opioids for comparison). Scenarios were considered where the proportion of patients prescribed opioids was allowed to vary from 30% up to 70%, all assuming a mean baseline PEG of 6 in the patients not prescribed opioids, a reduction in the PEG of 1 point for patients that are prescribed opioids, and a common standard deviation in PEG scores of 2 points [51]. All scenarios considered had at least 90% power to detect a difference of 1 point between groups with a total sample size of 630 patients (allowing for 30%-70% of the population to be prescribe opioids, meaning that with a range of 189 up to 441 patients prescribed opioids during the study period, there is ample power to detect differences between groups). All scenarios had at least 99% power to detect a 2-point difference on the PEG. We acknowledge that up to 40% of patients may drop out during the study due to the morbidity and mortality of patients in palliative care [58]. Data up until the point of attrition will be included in the analysis, and this has also been accounted for in our calculations.

#### Missing Data for Aim 1

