#### Aim 2: Data Analysis to Test Hypothesis 2b

To test our hypothesis that younger age, history of substance use disorder, and history of mood disorders will be associated with a greater risk of opioid misuse and use disorder, we will perform multivariable Cox regression analyses to assess the respective risk factors of interest. We will use a single prespecified model that includes age, history of substance use disorder, and history of mood disorders using baseline PRO data and chart review.

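### Aim 1 defines its confounders by statistical association, a rule that could admit consequences of pain or opioid use and drop real confounders

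*Protocol article*

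**What the plan says.** Under Aim 1: Data Analysis, PEG pain severity and pain interference at each time point are modelled with linear mixed-effects models, partly in order to "adjust for potential confounders". The fixed effects named are "Current opioid prescription, baseline pain severity or interference". The rest are given as "other confounders (ie, factors statistically associated with the exposure and outcome", and these too enter as fixed effects. The parenthesis opens with an *ie*, so it defines what counts as a confounder. It sets no causal criterion and no limit on when a factor is measured.

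Three other places bear on this:

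- Power Calculation for Aim 1 accepts that "in this study we will not have control over the ratio of patients allocated to the 2 comparison groups": opioid use is observed, not assigned.
- Assessments has the pain score taken every week ("The PEG will be collected weekly to provide longitudinal impact on pain severity, pain interference, and whether opioids precede any change in pain"). It adds "Additional monthly PROs will include information on mood", along with comorbidities and functioning, and some further items asked only of patients prescribed opioids.
- For hypothesis 2b the covariates are named in advance: "We will use a single prespecified model".

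**The concern.** A confounder is a common cause of exposure and outcome. A factor on the path from opioid to pain, or one affected by both, is also associated with both, so the stated rule cannot separate the three. The exposure is current prescription and the outcome is repeated through follow-up. A mood or functioning score taken after opioid start can plausibly be changed by pain, by opioids or by both. Adjusting for it alters the quantity being estimated.

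The rule can also fail the other way. A real common cause with only a weak association in this sample may not qualify and would be left out.

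With no randomisation, the coprimary comparison in hypothesis 1a rests on the adjustment set. The rule makes that set depend on the observed outcome data, and applied separately to severity and interference it could give two different sets.

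**Working it through.** **1. The plan's own figure.** Inputs from Power Calculation for Aim 1: difference 1 point, SD 2, N = 630, 30% to 70% prescribed opioids, up to 40% attrition. Two-sided alpha 0.05 is assumed.

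- N = 630, 30% prescribed (189 and 441): SE = 2 × √(1/189 + 1/441) = 0.174. Then 1/0.174 = 5.75, and power = Φ(5.75 − 1.96) = 99.99%.
- Worst case, all dropouts removed: N = 0.6 × 630 = 378. Power is 99.4%, 99.8% and 99.4% at 30%, 50% and 70% prescribed.

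The stated minimum of 90% holds. Power is not the issue; a large sample would estimate a wrongly adjusted quantity precisely.

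**2. Admitting a consequence.** Assume a true effect of −1 and one outcome per patient: y = 6 − A + e, SD(e) = 2. Let m = aA + cy + u, SD(u) = 1, where a is the direct effect of opioids on m and c the effect of pain on m. The within-group slope of y on m is s = 4c/(4c² + 1), and the coefficient of A given m is

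−1 − s(a − c).

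- *Consequence of pain only (a = 0).* This reduces to −(1 − r²), with r the within-group correlation of y and m: −0.75 at r = 0.5 and −0.51 at r = 0.7.
- *Common effect of opioids and pain.* When a exceeds c the estimate moves away from zero, as shown below.
- *Mediator.* If opioids raise m by a, and each unit of m lowers pain by g, the coefficient given m is −1 + ga.

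In simulation (1,000 replicates, N = 630, half prescribed opioids) the rule was read as p < 0.05 with exposure and p < 0.05 with outcome:

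| Variable | Assumed strengths | Formula | Passed the rule | Mean estimate under the rule |
|---|---|---|---|---|
| Common effect | a = 0.5, c = 0.15 | −1.19 | 98% | −1.19 |
| Common effect | a = 0.8, c = 0.15 | −1.36 | 100% | −1.36 |
| Common effect | a = 0.5, c = 0.25 | −1.20 | 81% | −1.18 |
| Common effect | a = 1.0, c = 0.25 | −1.60 | 100% | −1.60 |
| Mediator | a = 0.5, g = 0.6 | −0.70 | 100% | −0.69 |
| Mediator | a = 0.5, g = 1.0 | −0.50 | 100% | −0.50 |

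Leaving out the common effect gave −0.99 to −1.01.

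**3. Dropping real confounders.** Here K independent true confounders each raise both prescribing and pain. The assumed strengths are log odds of prescription and PEG points, per SD of the confounder. N = 630, true effect −1:

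| K | Log odds, points | Each kept | Estimate, rule | Estimate, full set | 95% CI coverage, rule | Coverage, full set |
|---|---|---|---|---|---|---|
| 5 | 0.15, 0.2 | 20% | −0.91 | −0.99 | 89% | 93% |
| 8 | 0.15, 0.2 | 21% | −0.85 | −0.99 | 84% | 96% |
| 8 | 0.2, 0.3 | 57% | −0.88 | −1.00 | 86% | 96% |
| 1 | 0.2, 0.3 | 57% | −0.98 | −0.99 | 94% | 95% |

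At N = 378 with 5 to 8 confounders, each was kept in 7% to 29% of studies, the estimate was −0.76 to −0.88 and coverage 79% to 90%. With one weak confounder the estimate was −0.97.

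**The case against.** The best defence is that this is one parenthesis in a condensed article. The candidate list, the timing and any cut-off commonly belong in the analysis plan, which is not shown, and the only covariate named is a baseline value. The absence of those details is indeed no finding, and no significance threshold is stated; the 0.05 used above is an assumption. But the article does state what makes a factor a confounder. An analysis plan that followed that definition would carry the fault with it.

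Several stronger readings are tempting and are not supported:

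- *The monthly measures all pass the test and will be adjusted for.* Nothing in the article shows this, and no follow-up measure is named as an Aim 1 covariate. The items asked only of opioid users could hardly enter a model of all patients. The practical risk lies with mood, functioning, comorbidities and coprescriptions.
- *Adjustment shrinks the effect by r².* That holds only for a variable that is a consequence of pain alone. A common effect of opioids and pain can move the estimate the other way.
- *The intervals will be too narrow.* This was not shown. The low coverage in step 3 came with a shifted estimate.
- *The article contradicts itself, because hypothesis 2b uses a prespecified model.* That model lists hypothesised risk factors, not a confounder set. It is a useful contrast, not an inconsistency.

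It also stands that baseline pain, an obvious driver of prescribing, is always in the model, and that losing one weak confounder costs little.

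**Conclusion.** The point holds as a fault in a stated rule. Followed literally, the Aim 1 definition could admit consequences of pain or opioid use and could leave out real confounders. The coprimary estimates could then be biased in either direction. That they will be biased does not follow from the article.

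The size is not determined by the documents. Across the assumed strengths, against a true −1.0, estimates ran from −0.50 to −1.60 when a consequence was admitted. At N = 630 they ran from −0.85 to −0.91 when the rule was applied to several weak confounders, and stayed at −0.98 with one. Shifts at the upper end are large against the 1-point difference the study is powered for. All of this rests on one outcome per patient, ordinary regression, a 0.05 cut-off and invented covariate strengths. It does not reproduce weekly repeated scores with a random subject effect. The change should be made, and it is cheap.

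**What to change.** Replace the parenthesis with a covariate list fixed in advance on causal or clinical grounds, drawn from what the study collects at baseline or before opioid start. Examples are age, site, cancer type, time since diagnosis, baseline PEG, baseline mood, functioning and comorbidity, and substance use history. State that every listed variable stays in whatever its association in the data, and that the list is the same for both coprimary outcomes.

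State also that variables measured after opioid start are not entered as ordinary covariates. For continuing users, the previous week's PEG or mood already reflects earlier opioid use. If such time-varying confounders are to be handled, use a method built for them, such as a marginal structural model, as a sensitivity analysis. Participants allows patients already prescribed opioids at enrolment, so the text should say how their baseline values are treated.

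Add disease progression, anticancer treatment or benzodiazepine use only where abstracted with dates before the exposure. Assessments does not show that the first two are collected, and Table 1 has benzodiazepine prescription reviewed only every six months.

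The cost is a wording change, some extra analysis work and possibly slightly wider intervals from keeping weak covariates. On the timetable in Results, follow-up runs to November 2026 with analysis finalised then, so the list can be fixed before the final analysis.

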### Participants

Patient participants must have an advanced solid cancer diagnosis, defined by the American Cancer Society as cancer that is unlikely to be cured [2]. An advanced cancer diagnosis can include patients who have distant metastases or a recurrence. Patient participants must be their own decision maker as determined by the electronic medical record (EMR) and enroll within 12 weeks of their advanced cancer diagnosis date. The research team will confirm an advanced cancer diagnosis using medical record documentation of pathology results or radiology and oncology documentation. We will recruit patient participants early after diagnosis so that we can understand opioid benefits, harms, and perspectives on opioid decision-making throughout the course of their advanced cancer (up to 2 years). Lived-experience perspectives related to opioid use in those with advanced cancer will be captured by qualitative interviews with a subset of enrolled patients, clinicians, and care partners.

We will specifically elicit information regarding long-term opioid use (ie, opioids for ≥90 consecutive days) and exclude patients on long-term opioid therapy before an advanced cancer diagnosis. Consistent with previous studies, we confirm opioid use in the medical record and will ask patient participants, “Did you take a strong prescription pain medication known as an opioid or narcotic for at least 90 days in a row during the past year? Examples of opioids include oxycodone, hydrocodone, hydromorphone, morphine, fentanyl, buprenorphine, methadone, and combination products such as oxycodone/acetaminophen.” This question is consistent with other commonly used research definitions of long-term or chronic opioid therapy [34,35]. Notably, this long-term opioid use definition also excludes individuals who are receiving methadone or buprenorphine/naloxone (suboxone) for the treatment of opioid use disorder, as the potential benefits and harms of opioid therapy in this population are unique and merit separate investigation [36]. This will allow us to understand the benefits, risk factors for harm, and perspectives on opioid decision-making when a patient with newly diagnosed advanced cancer begins an opioid or continues a newly initiated opioid.

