#### Assessments

Once patients have consented and enrolled in the study, data collection will include patient-reported outcomes (PROs), chart reviews, and interviews. Table 1 provides an overview of the study procedures and time frame.

**Table 1 table1:** Schedule of research activities.

Study stage	Screening and enrollment	Follow-up			
	Within 12 weeks of the date of diagnosis	Weekly after baseline	Monthly after baseline	Quarterly after baseline	Semiannually after baseline
Prescreening	✓				
Consent, screening, and contact information	✓				
Demographics and medical history	✓				
Baseline and demographics	✓				
Weekly 3-questions pain assessment: pain severity and inference		✓			
Monthly PRO^a^ assessment: mood, substance use, symptoms, and opioid misuse (Carey 2-year index)			✓		
Chart reviews: substance use, opioid misuse, and opioid overdose				✓	
Patient calls and chart review: Opioid prescription or dose, benzodiazepine prescription, over or under consumption of opioids					✓
TAPS^b^: substance use and opioid use disorder				✓	
Patient participants, care partners, and clinician interviews				✓	

^a^PRO: patient-reported outcome.

^b^TAPS: Tobacco, Alcohol, Prescription Medication, and Other Substance Use Tool.

Study staff will confirm patient demographics and cancer type from the medical record. Sites will use a chart abstraction tool to gather medication-related data every 6 months. Opioid dose will also be assessed through self-report by reading back the dose and instructions on the opioid bottle and confirmed in the EMR. Patient participants will consent to receiving a phone call from the study staff for pill counts during the latter part of the month of their prescriptions every 3 months.

Patient participants will complete baseline assessments and PROs electronically using REDCap, over the phone, or during clinic visits through a tablet by the study staff. If patient participants are unable to complete PROs, care partners will be permitted to complete the PRO assessments on behalf of the patient participants. We acknowledge that based on systematic reviews in oncology, there may be differences in patient-proxy reports, with proxies having a more negative view of the patient’s well-being [47].

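### The Aim 1 model names only a random subject effect for weekly PEG scores and a changing opioid exposure, so its model-based standard error would be too small if weekly residuals are serially correlated or pain slopes differ

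*Protocol article*

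**What the plan says.** Under Aim 1: Data Analysis, the protocol article offers linear mixed-effects models as its way of handling repeated measurements and confounding. The fixed effects are "Current opioid prescription, baseline pain severity or interference, and other confounders", and the sentence ends "while the subject will be included as a random effect". The outcomes are PEG severity and "pain interference (mean of 3 PEG items) at each time point". No random slope, residual covariance or robust standard error is named, and none is ruled out.

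Four other places bear on the point:

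- **Frequency (Assessments):** "The PEG will be collected weekly to provide longitudinal impact on pain severity". Table 1 agrees.
- **Duration (Participants):** follow-up lasts up to 2 years, so about 104 weekly scores per patient.
- **Changing exposure:** Participants describes a patient who "begins an opioid or continues a newly initiated opioid". Aim 3: Data Analysis expects opioids to be started and stopped during follow-up.
- **Exposure records (Assessments):** "Sites will use a chart abstraction tool to gather medication-related data every 6 months". Recorded opioid status may therefore be constant over blocks of up to 26 weeks.

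**The concern.** Read in the ordinary way, a random subject effect is a random intercept. It makes any two weeks from one patient equally correlated, whether 1 or 100 weeks apart, and gives all patients the same time course. Weekly pain scores are likely to be more alike when adjacent. Pain courses are also likely to diverge in a cohort that enrols patients with and without pain and follows them through advanced cancer.

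This matters because of the exposure. Opioid status can switch within a patient and then persist for weeks or months. The model counts each week of a spell as separate information about the opioid effect, although neighbouring residuals carry much of the same information. The reported standard error is then too small, confidence intervals on the coprimary outcomes are too narrow, and a null effect is declared significant too often, in either direction. Hypothesis 1a asks only whether opioids are associated with lower pain and sets no minimum size, so a small estimate with a falsely narrow interval could be reported as a finding.

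**Working it through.** **1. The plan's own power figure.** Inputs from Power Calculation for Aim 1: N = 630, 30% to 70% prescribed opioids, SD 2, difference 1 point, up to 40% attrition. Two-sided alpha 0.05 is assumed, because the article gives none.

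SE = 2 × √(1/n₁ + 1/n₂); power = Φ(1/SE − 1.96).

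- N = 630, 189 v 441: SE = 0.174, power 99.99%.
- N = 378 (40% lost), 30:70 split: SE = 0.224, power 99.4%. A 50:50 split gives SE = 0.206 and 99.8%.

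The stated 90% or more is consistent with this, and so is 99% or more for 2 points.

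**2. Why the standard error shrinks.** Let s be the share of within-patient variance that follows AR(1) with weekly correlation ρ, the rest being independent. For an exposure in long spells,

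(true SD / reported SE)² ≈ 1 + s × 2ρ/(1 − ρ).

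Taking s = ½ purely as an illustration:

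- ρ = 0.5: 1 + 0.5 × 2 = 2, ratio 1.41
- ρ = 0.8: 1 + 0.5 × 8 = 5, ratio 2.24
- ρ = 0.9: 1 + 0.5 × 18 = 10, ratio 3.16

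These are long-spell limits; shorter spells give less. For a ratio r, the expected rejection rate is 2 × {1 − Φ(1.96/r)}. For example, r = 1.40 gives 16%, r = 2.01 gives 33% and r = 2.62 gives 45%.

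**3. Simulation under no opioid effect.** 630 patients, 104 weekly scores, dropout reaching 40% by week 104. A REML random-intercept model with opioid, baseline PEG and linear time was tested at |z| > 1.96, with 500 runs per cell (Monte Carlo error about 1 to 2 points). Total variance was 4 (SD 2). The variance split, autocorrelation and exposure paths are assumptions; at AR(1) 0.5, a quarter of total variance was serially correlated. Cells show the false-positive rate, with true SD / reported SE in brackets.

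| Exposure pattern | No serial correlation | AR(1) 0.5 | AR(1) 0.8 | AR(1) 0.9 |
|---|---|---|---|---|
| Starts once, then stays on | 5% (1.02) | 18% (1.40) | 33% (2.01) | 45% (2.62) |
| Mixed never / always / episodic | 5% (1.04) | 14% (1.34) | 22% (1.70) | 30% (1.88) |
| Updated every 26 weeks | 5% (1.04) | 12% (1.34) | 35% (2.05) | 40% (2.35) |
| Never changes within patient | 7% (1.01) | 4% (0.93) | 7% (1.01) | 5% (1.03) |

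**4. Differing slopes only.** With slope SD 1 to 2 points over 2 years and no serial correlation (200 runs), the rate was 25% to 51% for start-once and 7% to 20% for mixed exposure.

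**5. Sensitivity to the assumptions.** With half the variance between patients and opioid spells of about 26 weeks (200 runs), the rates were 5%, 12%, 22%, 35% and 52% at autocorrelation 0, 0.3, 0.5, 0.7 and 0.9. A further start-once simulation gave about 7%, 22%, 48% and 68% at 0, 0.5, 0.8 and 0.9. The direction is stable; the size is not.

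**6. After the fix.** A patient-clustered sandwich standard error on the same model gave about 4% to 8% in every changing-exposure scenario of step 3.

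**7. Absolute size.** The largest true SD of the opioid coefficient in the step 3 and 4 scenarios was about 0.11 points. A 1-point effect is 1/0.11 ≈ 9 standard errors, so power is not at risk. Even 1.96 × 0.11 is only about 0.22 points.

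**The case against.** The strongest reply is that this treats silence as a statement. The sentence lists fixed and random effects; residual covariance and the variance estimator are separate choices, and a condensed article may leave them to an analysis plan that is not shown. This stands in part. The article excludes neither, so one can say only that the model as published names a single correlation term. But it does set out the coprimary model, for weekly data and a changing exposure, and following it literally has the consequence shown.

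The second reply is that the size is assumed. This stands in full. A reader might infer that the opioid standard error is certainly far too small and that the false-positive rate is several times 5%. The documents do not support that: they give no autocorrelation, no within-patient variance share and no length of opioid spells. The power section describes two groups of patients, and if opioid status hardly changed within patients there would be no inflation. The references to starting and stopping opioids make that unlikely, but how much patients switch is unknown.

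The third reply is that spurious effects would be small against the 1-point target. This also stands. It limits the clinical consequence but does not make the intervals correct.

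**Conclusion.** The point holds conditionally. As written, the Aim 1 model yields a valid model-based standard error for a changing opioid exposure only if weekly residuals are independent given the patient's intercept and all patients share one time course. Under assumed AR(1) of 0.5 to 0.9 with within-patient switching, false positives are about 12% to 45%, and the true SD is about 1.3 to 2.6 times the reported standard error. With independent residuals, or an exposure that never changes within patients, the rate stays near 5%.

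Two further inferences are not supported. The stated power is not undermined. Nor has the same been shown for Aim 2a: that section names no random-effect structure, and no calculation was run for it.

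**What to change.** In the Aim 1 analysis paragraph, state that inference on the opioid effect will use patient-clustered (sandwich) robust standard errors. Optionally add a serial residual correlation such as AR(1), or a random time slope per patient, to regain efficiency. The clustered standard error alone is enough to bring the error rate close to nominal.

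The cost is a sentence of text, slightly more model fitting and somewhat wider confidence intervals. No new data are needed. The Results section puts the end of follow-up and the final analysis at November 2026, so the wording can be settled before the final analysis.

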In general, linear mixed-effects models provide unbiased estimates when the data are assumed to be missing at random, meaning that the likelihood of a missing value is not related to the values of the outcome data (in this case, the assumption that missing values for pain are not related to the severity of the patient’s pain). The setting of this study will have two basic missingness problems: (1) data that are missing while the patient still lives, either because the survey could not be completed or the patient did not wish to complete the pain instrument; and (2) pain data that are missing because the patient is deceased. The missing at random assumption can never be fully confirmed, so we will perform three sensitivity analyses to see how our results vary under different approaches to handling the missing pain values: (1) multiple imputations; (2) imputing the worst pain value for patients that fail to complete the pain instrument for any reason (including death before the scheduled assessment); and (3) imputing the worst pain value for patients that fail to complete the pain instrument, but omitting patients that have died. It should be noted that in this patient population, death is an expected outcome and not necessarily a negative outcome with respect to end-of-life suffering and pain management.

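### The Aim 1 missing-data section misdefines missing at random, and its sensitivity analyses treat death as worst pain or may drop pre-death scores, with no departure from the assumption between none and the extreme

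*Protocol article*

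**What the plan says.** In the protocol article, Missing Data for Aim 1 justifies the primary model on the ground that "linear mixed-effects models provide unbiased estimates when the data are assumed to be missing at random". It then explains the assumption as "meaning that the likelihood of a missing value is not related to the values of the outcome data", adding in brackets that missing pain scores are taken to be unrelated to how severe the pain is.

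The section separates scores missing while the patient is alive from scores missing because of death. It accepts that the assumption cannot be confirmed and lists three sensitivity analyses:

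1. Multiple imputation, with nothing further said.
2. "imputing the worst pain value for patients that fail to complete the pain instrument for any reason (including death before the scheduled assessment".
3. "imputing the worst pain value for patients that fail to complete the pain instrument, but omitting patients that have died".

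It closes by noting that in this population "death is an expected outcome and not necessarily a negative outcome with respect to end-of-life suffering and pain management".

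Aim 1: Data Analysis makes current opioid prescription the exposure, with repeated PEG scores as the outcome. Power Calculation for Aim 1 expects up to 40% attrition from morbidity and mortality together, and says that data up to attrition enter the analysis.

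**The concern.** There are four difficulties.

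- **The definition is wrong.** Missing at random lets missingness depend on observed data, including earlier PEG scores. The section states a stricter condition, close to missing completely at random. With weekly PEG scores, dependence on earlier pain is the kind of missingness that the mixed model can accommodate, and the text rules it out.
- **Analysis 1 states no departure from the assumption.** If multiple imputation also assumes missing at random, its agreement with the mixed model does not test that assumption.
- **Analysis 2 scores death as maximal pain.** This sits badly with the section's closing sentence. It also creates outcome records at times when the exposure cannot be defined.
- **Analysis 3, read literally, removes whole patients.** Their observed scores before death would go too, and the comparison would be conditioned on surviving.

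With attrition of up to 40%, analysis 2 may track the pattern of deaths and skipped forms more closely than it tracks pain. Between no stated departure and the worst possible score, nothing shows how large a departure would change the conclusion on the coprimary outcomes.

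**Working it through.** **Inputs from the protocol article.** Power Calculation for Aim 1 gives mean PEG 6 without opioids, a 1-point reduction with opioids (mean 5), SD 2, N = 630, 30% to 70% prescribed opioids, and up to 40% attrition (0.40 × 630 = 252, leaving 378). Aim 1: Data Analysis gives a 0-10 scale, so the worst value is 10. The missing shares by group are **not** in the document and are assumptions.

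**The plan's own figure.** The article states at least 90% power for 1 point. I used one score per patient, the normal approximation and two-sided alpha 0.05 (assumed; none is stated), with power = Φ(1/SE - 1.96) and SE = 2·√(1/n1 + 1/n0).

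- N = 630, 30% on opioids (189 and 441): SE = 0.174, power 99.99%.
- N = 378, 30% on opioids: SE = 0.224, power 99.4%.
- N = 378, 50% on opioids: SE = 0.206, power 99.8%.

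The stated lower bound holds and does not depend on this point.

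**Effect of worst-value imputation at a single visit.** With missing share m, a group's mean becomes (1 - m)·μ + 10·m. The difference (opioid minus non-opioid) is therefore -1 + 5·m1 - 4·m0, where m1 is the opioid share and m0 the non-opioid share.

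| Missing, opioid / non-opioid | Opioid mean | Non-opioid mean | Difference (truth -1.0) |
|---|---|---|---|
| 40% / 40% | 0.6×5 + 4 = 7.0 | 0.6×6 + 4 = 7.6 | -0.6 |
| 50% / 30% | 0.5×5 + 5 = 7.5 | 0.7×6 + 3 = 7.2 | +0.3 |
| 40% / 20% | 7.0 | 0.8×6 + 2 = 6.8 | +0.2 |
| 20% / 40% | 0.8×5 + 2 = 6.0 | 7.6 | -1.6 |

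The difference is zero when m1 = (1 + 4·m0)/5. For m0 = 20% that is 36%.

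**Why the swing is so large.** Scoring 10 adds on average 10 - 5 = 5 points to each missing opioid score and 10 - 6 = 4 to each missing non-opioid score, against an effect of 1. A graded shift δ gives -1 + δ1·m1 - δ0·m0, if unshifted imputations are centred on 5 and 6. At 50%/30%, +2 points in both groups gives -1 + 1.0 - 0.6 = -0.6. Adding +2 in the opioid group alone gives -1 + 1.0 = 0, which is the tipping point for that split. The present plan jumps over this range.

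**Weight of a death in analysis 2.** Weekly PEG over 2 years is about 2 × 52 = 104 assessments. Read literally, a death at week 20 would add 104 - 20 = 84 scores of 10.

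**A small simulation, all settings assumed.** It used 60 runs, N = 630, half on opioids, 8 visits, within-patient correlation 0.5 and a true difference of -1. Dropout in the opioid group depended on the previous observed score, and final dropout was 27% versus 17%. This is missing at random, yet the article's definition excludes it. Mean estimates were:

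- mixed model: -0.98
- worst value: -0.74
- omitting every dropout (a stand-in for omitting those who died): -1.34

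When dropout depended instead on the current, unobserved score, the mixed model gave -1.10 and worst value -0.81.

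**The case against.** A reader might infer that none of the three analyses gives a usable check. The text does not support that. Analyses 2 and 3 both give worst pain to living non-completers, so they depart from missing at random and act as crude extreme bounds. Comparing them also shows how far death drives the result, in line with the two kinds of missingness that the section separates.

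Other points on that side also carry weight:

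- Multiple imputation with auxiliary variables would condition on more than the mixed model does. A condensed article may leave the imputation model to the analysis plan. What can be said is only that no departure is stated.
- The closing sentence about death may be a caveat on analysis 2 and the reason for listing analysis 3. A sensitivity analysis may use an assumption that its authors think extreme. The tension remains, because analysis 2 is not labelled that way.
- Analysis 3 may mean leaving out only assessments after death. The statement that data up to attrition are included favours this reading, but the words "but omitting patients that have died" refer to patients. This is an ambiguity, not an established loss of data.
- The group splits are assumed and run both ways: 20%/40% inflates the effect. A reader might infer that analysis 2 reverses the conclusion by construction, or that opioid-treated patients must have more missing data. The document gives no figure for either. The formula also describes one visit and two fixed groups, whereas the model uses weekly scores and an exposure that can change.
- The wrong definition does not by itself bias the primary estimate. The stated condition is stricter than the model needs, and in the simulation the model recovered -0.98.

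**Conclusion.** The point stands as one about a wrong definition and poorly fixed sensitivity analyses. It does not show that the primary analysis is invalid. The definition should be corrected whatever else is done. Analysis 1 states no departure from the assumption, analysis 2 mixes death with pain, and analysis 3 is ambiguous about pre-death scores. Analyses 2 and 3 test departures only at the score of 10.

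With the plan's means and assumed missing shares, worst-value imputation moves a true -1 to anywhere from -1.6 to +0.3 in the cases shown, through missingness alone. The direction depends on a split that the document does not give.

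A reader might also infer that analysis 3 discards most of the 40% lost. That cannot be computed, because the 40% combines morbidity and mortality and the share due to death is not stated.

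**What to change.** 1. Correct the definition: given the observed data, including earlier PEG scores and model covariates, missingness does not depend on the unobserved scores.
2. State that the target is pain while alive, using every observed week up to death and imputing nothing after it.
3. Reword analysis 3 so that only assessments after death are omitted and pre-death scores are kept.
4. Add delta-adjusted multiple imputation for weeks missed while alive, for example +0.5, +1 and +2 points, set separately by opioid status, and report the tipping point.
5. If analysis 2 is kept, label it an extreme bound that mixes death with pain. Deleting analyses 2 and 3 is not necessary, nor is a particular model such as GEE or a joint pain-survival model.

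The cost is revised wording and some extra analysis, with no new data and no change to the sample size or stated power. Follow-up is due to end by November 2026, so this should be settled before the analysis begins.
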